## 2. OBJECTIVES

### 2.1. Primary objective

**NOTE:** *In the event that malaria rates are lower in the year of the study the cross sectional survey, unblinding and analysis scheduled at 4½ months post Dose 3 will be delayed until approximately 245 children have experienced an episode.*

- For RTS,S/AS01E when administered as 3 doses intramuscularly on a 0, 1, 2-month schedule to children aged 5 to 17 months living in malaria-endemic areas:
  - to assess efficacy against clinical malaria disease meeting the primary case definition (detected on active and passive case detection) with *P. falciparum* over a period of 4½ months (starting two weeks post Dose 3).

Refer to Section 10.1 for definition of the primary endpoint.

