## **5.9. Active case detection (ACD) of Malaria**

Active Case Detection of malaria will commence two weeks post Dose 3.

At each visit the axillary temperature of each subject will be taken and if  $\geq 37.5^{\circ}\text{C}$  a blood slide and a rapid test (OptiMal®, Flow Incorporated, Oregon, USA) to determine malaria parasitemia will be taken.

If the child is documented to be febrile and the rapid test is positive, the field worker will give the child antimalarial chemotherapy and inform a study clinician. Mobile phones will be provided to study staff. Appropriate to the clinical features of the illness, transfer of children will be arranged to a health facility, if necessary. Amended 23 October 2006.

If the child is documented to be febrile and the rapid test is negative, antimalarial chemotherapy will not be administered by the field worker. A study physician will be informed. Appropriate to the clinical features of the illness, the child's parent(s)/guardian(s) will be advised to attend their nearest health facility to be reviewed by clinically qualified personnel (medical or nursing) or transfer will be arranged to the secondary care facility.

If the parents/guardians report the child has had a fever but the axillary temperature is  $< 37.5^{\circ}\text{C}$ , the field worker will revisit the child between 6 to 12 hours later to recheck the temperature and if the temperature is measured as  $\geq 37.5^{\circ}\text{C}$  a blood slide and rapid malaria test will be taken. If the test is positive, the child's case will be managed as above.

If no fever is documented at the revisit, a study physician will be informed. Appropriate to the clinical features of the illness, the child's parent(s)/guardian(s) may be advised to attend their nearest health facility to be reviewed by clinically qualified personnel (medical or nursing), or transfer will be arranged to the secondary care facility or on a study physician's advice, no further action is required. The parent(s)/guardian(s) will be informed that if they have concerns, they may always attend their nearest health facility to have their child reviewed by clinically qualified personnel.

Treatment will be indicated by rapid test result. Blood slides for parasitemia will not be read in real time to guide case management routinely. Blood slides will always be taken in duplicate.

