#### **5.10. Passive case detection (PCD) of malaria**

When a subject is presented to a health facility within the study areas, the child will be reviewed by clinically qualified personnel (medical or nursing) and treated as required. The temperature will be recorded and if  $\geq 37.5^{\circ}\text{C}$  a rapid test and blood slide will be performed. Antimalarial medication will be recorded and study personnel will be informed.

When a subject presents spontaneously to a fieldworker, the axillary temperature will be taken and if  $\geq 37.5^{\circ}\text{C}$  a blood slide and a rapid test (OptiMal®, Flow Incorporated, Oregon, USA) to determine malaria parasitemia will be taken.

If the child is documented to be febrile and the rapid test is positive, the field worker will give the child antimalarial chemotherapy and inform a study clinician. Mobile phones will be provided to study staff. Appropriate to the clinical features of the illness, transfer of children will be arranged to a health facility, if necessary. If the child is afebrile or the rapid test is negative, the case will be discussed with a study physician. Appropriate to the clinical features of the illness, the child's parent(s)/guardian(s) will be advised to attend their nearest health facility to be reviewed by clinically qualified personnel (medical or nursing) or transfer will be arranged to the secondary care facility. Amended 23 October 2006.

Blood slides for parasitemia will not be read in real time to guide case management routinely. Blood slides will always be taken in duplicate. Full details for PCD and operational methods will be given in site-specific SOPs.

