### **10.5. Case Definitions for Malaria**

**Primary malaria case definition** *P falciparum* infection > 2 500 parasites per  $\mu$ L in a child with a documented fever  $\geq 37.5^{\circ}\text{C}$  (axillary) detected by ACD or PCD.

**Secondary malaria case definition** *P falciparum* infection > 0 parasites per  $\mu$ L in a child with a documented fever  $\geq 37.5^{\circ}\text{C}$  (axillary) detected by ACD or PCD.

Amended 23 October 2006

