## **10.6. Estimated sample size**

### **10.6.1. Power Calculations**

The final analysis is projected to occur after the completion of 4 months of surveillance, at which time it is assumed that 36% of children in the control group will have been affected by a malaria episode. Assuming a true vaccine efficacy of 30% and an attack rate of 36% in controls (corresponding to an attack rate of 25.2% in vaccinees), a sample size of 400 evaluable subjects per group has 90% power to detect a difference between groups using a 2-sided Fisher exact test at 5% significance level. The final analysis is projected to occur after the completion of 4 months of surveillance, at which time it is assumed that 36% of children in the control group will have been affected by a malaria episode. However, in the event that malaria rates are lower in the year of the study, the unblinding and analysis will be delayed until approximately 245 children have experienced an episode ( $400 \times 36\% + 400 \times 25.2\% = 245$ ). This analysis will also have 90% power.

The assumption of 36% attack rate in controls is based on epidemiological data collected at the two sites. In Kilifi the proportion of children aged 12 to 18 months olds affected by a malaria episode using the same ACD methodology as proposed in this document over the same time frame in 2005 was 37% (personal communication [name]). In Korogwe the case rate was 34% determined in children aged 5 to 17 months in Mkokola village (10 km from Korogwe) by Passive Case Detection at village level (personal communication [name], [name]).

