#### **10.9.4. Calculation of time at risk**

For efficacy endpoints, the time at risk will be counted in days, and expressed as person years at risk (days/365.25).

For each subject in the Total Cohort, time at risk begins 14 days after Dose 3 for those that received Dose 3 or 2½ months after Dose 1 (Day 75) otherwise. For the According to Protocol Cohort, time at risk begins 14 days after Dose 3.

The time at risk will end whenever one of the following conditions happen first: endpoint definition met, loss of follow up, emigration from the study area, withdrawal, death, end of follow-up period.

The time at risk will take into account absences from the study area and anti-malaria drug therapy. Absences from the study area of 1 week or more will be recorded in multiples of 1 week. The date of departure will be documented. Similarly, if treatment for malaria is administered, the subject will not be considered susceptible to malaria infection for the longest duration of the combination of drugs the subject could receive for this episode as follows: 28 days if received Coartem®, 28 days if having received sulfadoxine-pyrimethamine and 7 days if having received quinine alone.

If an episode is detected during a period of time not counting for the time at risk it will not be included in the analysis, however a table will be presented showing the number of such episodes not included in the analysis.

Episodes will be included in the analysis only if the subject is identified properly showing his/her ID Card at the contact with the health facility. Only blood slides that complete the reading process according to SOP will be considered in the establishment of endpoints.

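### The episode-inclusion rule in Section 10.9.4 ties the ID card to a health-facility contact, which contradicts a case definition that also counts episodes found by field workers

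*Protocol*

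**What the plan says.** The last paragraph of Section 10.9.4 sets a condition for every efficacy episode: "Episodes will be included in the analysis only if the subject is identified properly showing his/her ID Card at the contact with the health facility". It makes no exception for episodes found elsewhere.

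Other sections describe detection more broadly:

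- **Section 2.1** assesses efficacy against malaria "detected on active and passive case detection".
- **Section 10.5** defines both the primary and the secondary case by parasite density "in a child with a documented fever", "detected by ACD or PCD". Neither definition mentions a facility or a card.
- **Section 5.9**: at a home visit with fever and a positive rapid test, "the field worker will give the child antimalarial chemotherapy and inform a study clinician". Beyond that, "transfer of children will be arranged to a health facility, if necessary".
- **Section 5.10** counts contact with a field worker as passive detection: "When a subject presents spontaneously to a fieldworker, the axillary temperature will be taken", followed by a slide and rapid test if the child is febrile.
- **Section 5.14** lists a card check at the field-worker visits and at all passive-detection visits.
- **Section 10.6.1** bases the 36% control attack rate on two figures. The Kilifi proportion, "using the same ACD methodology as proposed in this document over the same time frame in 2005 was 37"%, was counted with active detection. The Korogwe figure, 34%, came from passive detection at village level.

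Section 10.9.4 promises a table of excluded episodes only for those that fall in time not counted as at risk. It promises none for episodes that fail the card condition.

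**The concern.** A child found at home with fever and a density well above 2,500 parasites per µL, treated by the field worker and not transferred, is a primary case under 10.5. The same child has no facility contact at which to show a card, so the literal wording of 10.9.4 excludes the episode. A child brought to a field worker is in the same position. The two sections cannot both be applied as written, and two programmers could build different primary datasets from them.

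The narrower reading leaves a smaller problem. A child seen and slide-confirmed at a facility, but without the card, is excluded even when identity could be established from records the study holds.

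What is at stake is the number of countable first episodes, and with it power or the date of the analysis. The sample size presumes that actively detected cases count.

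**Working it through.** **Inputs from Section 10.6.1:** 400 evaluable children per group; attack rates 36% (control) and 25.2% (vaccine); two-sided Fisher exact test at 5%; stated power 90%; about 245 children with an episode.

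**Input not in the protocol:** *f*, the share of first episodes lost to the card rule. No section gives the place of detection or how often cards are shown, so *f* is an assumption shown over a range and taken as equal in both arms.

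**Step 1: reproduce the plan.**

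Children with an episode = 400 × 0.36 + 400 × 0.252 = 144.0 + 100.8 = 244.8.

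Power = Σ over (x₁, x₂) of Bin(x₁; 400, 0.36) × Bin(x₂; 400, 0.252) × 1[Fisher p ≤ 0.05] = 0.902. Both stated figures reproduce.

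**Step 2: apply the loss.** Replace the rates by 0.36(1 − f) and 0.252(1 − f) and repeat.

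| f | Control rate | Vaccine rate | Children counted | Exact Fisher power |
|---|---|---|---|---|
| 0% | 36.0% | 25.2% | 244.8 | 90.2% |
| 10% | 32.4% | 22.7% | 220.3 | 85.3% |
| 20% | 28.8% | 20.2% | 195.8 | 79.1% |
| 30% | 25.2% | 17.6% | 171.4 | 71.6% |
| 50% | 18.0% | 12.6% | 122.4 | 52.9% |

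**Step 3: effect on the estimate.** The risk ratio is 0.252(1 − f) / 0.36(1 − f) = 0.70 at every f, so equal loss leaves efficacy at 30% on this scale.

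**Step 4: how far the table depends on the model.** It assumes that no later episode replaces a dropped one. A simulation with a constant hazard over 122 days, a 28-day gap after each treated episode and replacement allowed gives 223 children and 87% power at 10% loss, and 129 children and about 60% at 50%. Rate-based efficacy stays at about 35% at every loss level. The table is therefore somewhat pessimistic, but the direction is the same.

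**Step 5: the event trigger.** Sections 10.1, 10.6.1 and 10.10 delay unblinding and analysis until about 245 children have had an episode if malaria rates are low. The protocol does not say whether these must be episodes that pass 10.9.4. If they must, lost episodes postpone the analysis and the power in Step 2 is not lost. If any episode meeting the case definition counts towards 245, the analysis goes ahead with fewer usable events, as in the table.

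**The case against.** The strongest reply is that nobody would apply the sentence to home-detected cases. Doing so would empty Section 5.9 and contradict 10.5, and the card is already a listed check at field-worker and passive-detection visits. On this view 10.9.4 only sets the identification standard at facilities. Much of this stands: it is the more coherent reading, and the conflict does not prove that actively detected cases would be dropped. But the sentence opens with all episodes and names only the health facility, so the wording does not deliver that reading.

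A strict identification rule also protects against attributing an episode to the wrong child. That purpose is sound and the fix keeps it.

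A reader might infer four stronger things that the documents do not support:

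- **That most episodes would be lost.** No loss fraction is documented, and the large ones need the literal reading.
- **That an excluded child stays in the denominator as event-free.** Exclusion for want of a card is not a listed end of time at risk, but meeting the endpoint definition is. The excluded episode might therefore end time at risk without counting as an event. The protocol does not settle this.
- **That efficacy is biased.** That needs unequal loss. For example, losing 10% of control and 20% of vaccine episodes would give 1 − (0.252 × 0.8)/(0.36 × 0.9) = 37.8%. Nothing in the protocol suggests unequal loss, and the primary phase is blind to parents and evaluators.
- **That carers of severely ill children forget the card more often.** No section bears on this.

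**Conclusion.** The point holds as a contradiction in an explicit rule. Taken literally, Section 10.9.4 conflicts with Sections 2.1, 5.9, 5.10 and 10.5 and with the Kilifi basis of the sample size. Taken narrowly, it still discards genuine facility episodes when the card is missing, with no tabulation of how many.

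The size cannot be known from the protocol. With equal loss of 10%, 20% or 50%, power falls from 90% to about 85%, 79% or 53%, or the analysis is delayed, depending on what the 245-child trigger counts. These figures illustrate the effect of an assumed loss and do not predict it. Under equal loss the harm is to power, precision or timing, and the efficacy ratio is not distorted. The wording should be corrected because it governs which episodes enter every clinical-malaria endpoint and the correction is cheap.

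**What to change.** Replace the sentence in 10.9.4 with:

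> An episode detected at any ACD, field-worker or health-facility contact will be included if the subject's identity was verified at that contact by the study ID card or, if the card was not shown, by matching date of birth and household to the clinic form, with the match completed blind to allocation. Episodes whose identity cannot be verified are excluded and tabulated by group.

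State also that the 245-child trigger counts episodes included under this rule. Add a sensitivity analysis restricted to card-verified episodes.

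The fallback identifiers are limited to date of birth and household because Section 5.2.2 records these on the clinic form. The photograph is described only as attached to the card, so it cannot stand in for a card that was not brought.

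The cost is a sentence or two of text and a blinded record match for contacts without a card. The downside is a small risk of accepting a misidentified child, which the card-only sensitivity analysis covers. No clinical procedure changes.

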#### **10.9.5. Covariates**

The risk for malaria and development of clinical disease depends on numerous factors related to the parasite, host and vector biology. In addition to demographic data, covariates to be collected in this study will include:

- study center.
- bednet use.
- residual spraying
- geographical area.
- distance from health center.

- altitude above sea level of subject's permanent residence.

Covariates included in the adjustment for efficacy will be defined in the Report Analysis Plan. Amended 23 October 2006.

## **10.10. Final analyses**

The final analysis will be conducted on data collected until Clinic Visit 6. The study will continue in a single-blind manner. This additional information will be appended to the study report.

In the event that malaria rates are lower in the year of the study the unblinding and analysis following Clinic Visit 6 will be delayed until approximately 245 children have experienced an episode. This analysis will have 90% power assuming true vaccine efficacy to be 30%.

### **10.10.1. Analysis of efficacy**

Analysis of efficacy will be performed on the ATP Cohort for Efficacy and Total Cohort. Vaccine efficacy endpoints:

- time to first/only case of malaria.
- multiple events of malaria.
- parasite prevalence and density.
- hemoglobin values.

will be analyzed according to methods described in Section 10.9.

### **10.10.2. Analysis of demographics/baseline characteristics**

Demographic characteristics (age, gender) and baseline covariates of each study cohort will be tabulated.

The mean age (plus range and standard deviation) by gender of the enrolled subjects, as a whole, and per group, will be calculated.

The distribution of subjects enrolled by study site will be tabulated as a whole and per group.

### **10.10.3. Analysis of immunogenicity**

The primary analysis will be based on the ATP cohort for the analysis of immunogenicity. If the percent of enrolled subjects excluded from this ATP cohort is more than 5%, a second analysis based on the Total Vaccinated Cohort will be performed to complement the ATP analysis.

**10.10.3.1. Anti-CS antibodies**

The percentage of subjects seropositive for anti-CS (proportion of subjects with anti-CS antibody titers greater than or equal to 0.5 EU/mL) with 95% CI will be determined at each blood sampling time point. Antibody titers will be summarized by GMT with 95% CI at all time points at which serological samples are taken. Tables will be generated by vaccine group and by protection status (protected subjects are those recipients of RTS,S/AS01E who are not diagnosed with malaria meeting the primary case definition within the 4½ month ACD period). Antibody titers after the third dose will also be investigated using reverse cumulative curves. Comparisons between protected and non-protected may be performed using Wilcoxon Rank Sum tests.

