**Immunogenicity**

- Anti-CS antibody titers prior to vaccination, 1 month post Dose 3 and 4½ months post Dose 3.
- Anti-HBs antibody titers prior to vaccination and 1 month post Dose 3.
- Frequency of CD4+ and CD8+ CS-specific T-cells expressing at least two of the following: IL-2, CD40L, TNF-α and IFN-γ prior to vaccination and 1 month post Dose 3.

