#### **10.7.3. According-to-Protocol (ATP) cohort for analysis of immunogenicity**

The ATP cohort for analysis of immunogenicity will include all evaluable subjects (i.e. those meeting all eligibility criteria, complying with the procedures defined in the protocol, with no elimination criteria during the study) for whom data concerning immunogenicity endpoint measures are available.

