#### **10.11.3.1. Anti-CS antibodies**

The percentage of subjects seropositive for anti-CS (proportion of subjects with anti-CS antibody titers greater than or equal to 0.5 EU/mL) with 95% CI will be determined at Clinic Visit 7 *and Clinic Visit 9*. Antibody titers will be summarized by GMT with 95% CI. Tables will be generated by vaccine group and by protection status (protected subjects are those recipients of RTS,S/AS01E who are not diagnosed with malaria meeting the primary case definition within the 4½ month ACD period). Comparisons between protected and non-protected may be performed using Wilcoxon Rank Sum tests.

*Amended 17 April 2008*

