### 10.11.3.3. Frequency of CD4+/CD8+ CS-specific T-cells

The frequency of CD3+ CD4+/CD8+ T-cells specific to CS will be identified as CD4/CD8 + T-cells expressing at least two cytokines amongst CD40L, IL-2, TNF- $\alpha$  and IFN- $\gamma$  upon short-term in vitro stimulation with a pool of peptides covering the vaccine CS portion. Results will be expressed as CS-specific CD4/CD8 T-cells per million respectively of CD4 or CD8+ T-cells. Descriptive statistics (N, minimum, Q1, median, Q3, maximum, mean, standard deviation) will be tabulated by group and protection status at Clinic Visit 7 (protected subjects are those recipients of RTS,S/AS01E who are not diagnosed with malaria meeting the primary case definition within the 4½ month ACD period). Analysis by protection status will be limited to recipients of RTS,S/AS01E. Results will also be presented graphically by box plots. Between group comparisons and between protection status comparisons will be performed by non-parametric Wilcoxon Rank Sum tests. Within group comparisons (i.e. comparing post versus pre timepoint within the RTS,S group) will be performed by Wilcoxon Signed Rank test for paired samples.

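### The protection label used to split immune responses ignores incomplete follow-up and stays fixed at 4½ months, so later titres are compared by an outcome that is already past and, for many children, out of date

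*Protocol*

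**What the plan says.** Section 10.10.3.1 defines protected subjects as "those recipients of RTS,S/AS01E who are not diagnosed with malaria meeting the primary case definition" in the 4½-month active case detection period. Sections 10.10.3.2 to 10.10.3.4 and 10.11.3.1 to 10.11.3.3 repeat the definition. None of them sets a minimum time under observation.

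On timing, Section 10.10.3.1 says "Antibody titers will be summarized by GMT with 95% CI at all time points at which serological samples are taken", with tables by vaccine group and by protection status. The anti-CS endpoint in Section 10.2 reads "Anti-CS antibody titers prior to vaccination, 1 month post Dose 3 and 4½ months post Dose 3", so the last of these samples falls at the end of the outcome window. In the annex, Section 10.11.3.1 takes anti-CS at Visits 7 and 9 and says "Tables will be generated by vaccine group and by protection status". Anti-HBs and T-cells at Visit 7 are handled the same way.

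On testing, the antibody sections are permissive: "Comparisons between protected and non-protected may be performed using Wilcoxon Rank Sum tests". The T-cell sections are not: "Between group comparisons and between protection status comparisons will be performed by non-parametric Wilcoxon Rank Sum tests".

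The main immunogenicity set is the ATP cohort, meaning subjects "complying with the procedures defined in the protocol, with no elimination criteria during the study) for whom data concerning immunogenicity endpoint measures are available". Section 10.10.3 adds a Total Vaccinated Cohort analysis if more than 5% of enrolled subjects are excluded from it.

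**The concern.** Two features of the label cause trouble.

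First, it turns a censored time-to-event outcome into a yes/no status. Section 10.9.4 ends time at risk at loss to follow-up, emigration, withdrawal or death. The protection label has no counterpart, so a child who left with a titre but before the window closed is counted as a success.

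Second, it is frozen at 4½ months. The Visit 6 anti-CS titre comes after the outcome that defines the split, and the Visit 7 and 9 samples come well after it. A difference at those visits could run from malaria or its treatment to the response, not the other way round. A child with a first episode in, say, month 9 still sits in the protected column of the Visit 7 table. This is awkward because Section 1.6.4 justifies the Visit 9 serum by a possible link between duration of protection and duration of immunogenicity. A status fixed at 4½ months cannot speak to duration.

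At stake is the reading of the immune-response tables and tests, not the efficacy claim.

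**Working it through.** **The plan's own figures (Section 10.6.1).** The inputs are 400 evaluable per group, a 36% control attack rate and 30% efficacy, so the vaccinee rate is 0.36 × 0.70 = 25.2%.
- Cases: 400 × 0.36 + 400 × 0.252 = 244.8, matching the stated 245.
- Two-sided Fisher exact power at 5%, by full enumeration: 90.2%, matching the stated 90%.
- The protocol gives no figure for the protection-status analysis, so the rest follows from these rates.

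**Size of the groups.** Among 400 vaccinees, 400 × 0.252 = 100.8 are expected cases and 299.2 would be called protected.

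**Later malaria among the protected.** Assume a constant hazard over the four-month window: h = −ln(1 − 0.252)/4 = 0.0726 per month. The window closes about 4½ months after Dose 3, leaving 7.5 months to month 12. The share with a first case by then is 1 − exp(−h × 7.5).

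| Assumed later hazard | Share of protected | Children of 299 |
|---|---|---|
| A quarter of h | 13% | 38 |
| Half of h | 24% | 71 |
| h unchanged | 42% | 126 |
| Control hazard, −ln(0.64)/4 = 0.1116 | 57% | 170 |

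Counting 12 months from the start of time at risk adds two further four-month periods, which gives 1 − 0.748² = 44%.

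**Incomplete follow-up.** Section 10.7.3 states no minimum time at risk, and Table 4 gives no interval for Visit 6. Planned loss is 445 − 400 = 45 per group (45/445 = 10.1%), above the 5% trigger. A Total Vaccinated Cohort analysis is therefore likely if that loss also applies to the immunogenicity cohort. As an upper bound, let all 45 leave evenly over the four-month window.
- Average probability of no case before leaving: 0.252/(4 × 0.0726) = 0.868. Labelled protected: 45 × 0.868 ≈ 39.
- Of these, would have become cases had they stayed: 45 × (0.868 − 0.748) ≈ 5.
- Share of the protected group: 39/(39 + 299) ≈ 12%.

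The true share is smaller, because children who left before Visit 5 have no post-Dose 3 titre.

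**Order of sample and outcome.** Case detection starts 14 days after Dose 3 (Section 5.9). Visit 5 is 21 to 42 days after Dose 3 (Table 4). Expected vaccinee cases before Visit 5 are 400 × [1 − exp(−h × t)], with t the months from day 14.
- Day 21: 7 cases (7% of 100.8).
- Day 30: 15 cases (15%).
- Day 42: 26 cases (26%).

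The baseline sample precedes every counted case and the 1-month sample precedes most. The Visit 6, 7 and 9 samples fall at the end of the window or after it.

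**Precision of the proposed model.** The detectable hazard ratio per SD at 80% power is exp[−(1.96 + 0.84)/√D]. With D = 101 it is 0.76. With D = 86, after dropping the 15 early cases, it is 0.74.

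**The case against.** Much can be said for the plan. These are secondary, tertiary or exploratory summaries, and Section 2 lists no correlate-of-protection objective. The antibody tests are optional. In the final analysis, anti-HBs and T-cells by status use only the baseline and 1-month samples, so the Visit 6 anti-CS titre is the only one there that follows its outcome. The annex states its 4½-month label openly, and transmission is seasonal, so a constant hazard is a rough device. All of this stands, and it limits the weight of the point. It does not remove it: the tables by status will be produced, the T-cell tests are mandatory, and the label is fixed in the protocol.

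Three stronger readings are tempting and not supported.
- *Any early drop-out is counted as protected.* A child lost in the third week after Dose 3 will usually have no Visit 5 sample, Section 10.8 does not replace missing titres, and the ATP definition may remove others. A child with a Visit 6 titre attended Visit 6. The problem is confined to children lost between Visits 5 and 6, mainly in the Total Vaccinated Cohort, and the 12% above is a ceiling.
- *Differences between sites produce false titre-protection links.* Simulation (400 vaccinees, SD 0.5 log10, 10% drop-out) gives Wilcoxon false-positive rates of 9 to 13% with assumed attack rates of 37% against 15 to 20% and a GMT ratio of 1.5. Section 10.6.1 gives 37% and 34%, and nothing in the protocol supports that GMT ratio. At 37% and 34%, even with the ratio of 1.5, the rate is 5.0%. No inflation is shown.
- *All the titres compared post-date the outcome.* The baseline and most 1-month titres do not.

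**Conclusion.** The point holds in a limited form. The label does not require complete follow-up, it splits the 4½-month anti-CS titre by an earlier outcome, and in the annex it keeps calling children protected after they have had malaria. The last effect is the largest: about 42 to 44% of the protected group by 12 months if the planned four-month rate continued, and 13 to 57% across the hazards tried. The hazards after 4½ months are assumptions; that such children keep the label follows from the text. The drop-out effect is small: at most about 5 would-be cases mislabelled if losses are spread evenly over the window. The primary efficacy analysis is untouched. The change is worth making because the annex tables invite conclusions about lasting protection that this split cannot support.

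**What to change.** Among RTS,S/AS01E recipients, replace the protected/non-protected Wilcoxon comparisons of the 1-month post Dose 3 antibody and ICS responses with a Cox model.
- Predictor: log10 of the Visit 5 response, as a continuous variable.
- Stratify by study center. This is ordinary good practice with two sites and does not rest on any demonstrated confounding.
- Start time at risk at the Visit 5 sample (landmark or delayed entry) and exclude children with an earlier case. The Section 10.9.4 start, 14 days after Dose 3, would place cases before the predictor was measured.
- Censor drop-outs by the Section 10.9.4 rules.

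For Visits 6, 7 and 9, report titres by vaccine group only, or relate them to malaria occurring after the sample.

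The cost is the roughly 15% (7 to 26%) of vaccinee cases that precede Visit 5, with little loss of precision: the detectable hazard ratio per SD moves from 0.76 to 0.74. No new samples or visits are needed.
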